## Abstract

**Background:**

Persecutory delusions are the most common type of delusions in psychosis and present in around 10–15% of the general population. Persecutory delusions are thought to be sustained by biased cognitive and emotional processes. Recent advances favour targeted interventions, focussing on specific symptoms or mechanisms. Our aim is to test the clinical feasibility of a novel psychological intervention, which manipulates biased interpretations toward more adaptive processing, in order to reduce paranoia in patients.

**Methods:**

The ‘Cognitive Bias Modification for paranoia’ (CBM-pa) study is a feasibility, double-blind, randomised controlled trial (RCT) for 60 stabilised outpatients with persistent, distressing paranoid symptoms. Patients will be randomised at a 50:50 ratio, to computerised CBM-pa or a text-reading control intervention, receiving one 40-min session per week, for 6 weeks. CBM-pa involves participants reading stories on a computer screen, completing missing words and answering questions about each story in a way that encourages more helpful beliefs about themselves and others. Treatment as Usual will continue for patients in both groups. Patients will be assessed by a researcher blind to allocation, at baseline, each interim session, post treatment and 1- and 3-month follow-up post treatment. The primary outcome is the feasibility parameters (trial design, recruitment rate and acceptability) of the intervention. The secondary outcomes are clinical symptoms (including severity of paranoia) as assessed by a clinical psychologist, and ‘on-line’ measurement of interpretation bias and stress/distress. The trial is funded by the NHS National Institute for Health Research.

**Discussion:**

This pilot study will test whether CBM-pa has the potential to be a cost-effective, accessible and flexible treatment. If the trial proves feasible and demonstrates preliminary evidence of efficacy, a fully powered RCT will be warranted.

**Trial registration:**

Current Controlled Trials ISRCTN: 90749868. Retrospectively registered on 12 May 2016.

**Electronic supplementary material:**

The online version of this article (doi:10.1186/s13063-017-2037-x) contains supplementary material, which is available to authorized users.

## Background

Psychosis is one of the most disabling mental health conditions, with a lifetime rate of 3.5% [1], and it is associated with significant distress, unemployment, impaired social functioning, physical ill health and suicidal ideation [2]. Persecutory delusions are the most frequent and clinically significant symptoms of psychosis. They are associated with considerably more distress than other types of delusion [3]; are most likely to be acted upon [4] and represent a strong predictor of hospitalisation [5]. Over one third of all UK psychiatric patients suffer from persecutory delusions, and they are reported in depression [6], bipolar disorder [7], posttraumatic stress disorder [8], anxiety [9], and with the highest prevalence and greatest intensity in schizophrenia [10]. A significant proportion of patients suffering from persecutory delusions, continue to experience distressing symptoms despite available treatments [11, 12].

Previous research showed that the distribution of paranoid thinking in the general population is continuous, ranging from social evaluative concerns (e.g. fears of rejection) to severe threat (e.g. people trying to cause significant harm), indicating a hierarchical structure to paranoia [13–17]. Persecutory delusions are the extreme point on the continuum of paranoid belief, and are likely to be perpetuated by biased cognitive-emotional processes [13–18].

‘Cognitive bias’ refers to selective processing of information matching the core content of the pathology of a disorder; for example, individuals with threat-related persecutory delusions interpret emotionally ambiguous information as threatening. Savulich et al. [17] point out that ‘cognitive deficits are impairments in cognitive functioning at the global level, whereas cognitive biases involve the selective processing of pathology-congruent information with the potential to confirm matching pathological beliefs’ (p. 516).

For example, general problems in attentional functioning or working memory are cognitive deficits, but repeatedly attending to a certain type of maladaptive stimulus, in preference to more benign alternatives, or consistently interpreting emotionally ambiguous information in one (maladaptive) direction would both be examples of a cognitive bias (in attention and interpretation, respectively). Furthermore, recent theoretical thinking in psychosis is attempting to integrate cognitive models of threat appraisals with models based on neural findings in areas such as the amygdala, the insula, the hippocampus, the anterior cingulate cortex and the prefrontal cortex [19].

These cognitive biases help to cause and maintain a range of psychopathologies [20, 21], including psychosis/delusions [3]. Cognitive therapy can work by changing underlying biases so that these maintaining mechanisms are no longer present and, ideally, patients instead acquire biases that promote wellbeing [22, 23] and, as a result, symptoms resolve. However, the Schizophrenia Commission report that the NICE-recommended psychological therapy for psychosis, cognitive behavioural therapy (CBT), is received by only 1 in 10 of those who could benefit and has shown only moderate effect sizes for delusions [24, 25]. New directions in treatments for delusions emphasise briefer, targeted interventions, with a focus on putative causal factors, such as cognitive biases [26, 27].

Here, we aim to test the feasibility of a new targeted psychological intervention ‘Cognitive Bias Modification for paranoia’ (CBM-pa) which uses a computerised task to manipulate biased interpretations of emotionally ambiguous information, with the aim of promoting more adaptive processing. CBM is a validated, theory-driven treatment with an established methodology [28]. CBM has arisen directly from laboratory research into the nature of the cognitive biases across a range of disorders. Two high-impact articles have alerted the research community to CBM’s potential as a novel treatment [29, 30], with evidence of its efficacy in reducing pathological beliefs, symptoms and stress vulnerability in anxiety and depression [31]. More cautionary reports have also pointed out that efficacy varies across studies [32] and researchers need to proceed with caution in applying CBM to new clinical populations, ensuring that the necessary basic research has been conducted prior to implementing CBM methodologies.

The first necessary step in this basic research is to identify the relevant naturally occurring biases and how they present in the target disorder. The CBM methodology can then be adapted to be specifically relevant for that target disorder. Previous studies suggest that a negative interpretation bias occurs in those with elevated vulnerability to paranoia, and that this bias may be strongest for material matching paranoid beliefs both in nonclinical and clinical samples [17, 18]. Specifically, interpretation of everyday information as personally threatening has been found to be related to the onset and maintenance of paranoid symptoms [33]. Therefore, an intervention targeting these biases offers potential to reduce distressing paranoia. Moritz and colleagues [34], have pioneered ‘metacognitive training’ (MCT) for a range of social-cognitive biases found in psychosis. Using group training, they obtained improvements in delusions in a large randomised controlled trial (RCT). Previous studies, using computerised treatment targeting reasoning bias in patients with persecutory delusions, also demonstrated the effectiveness of a brief reasoning intervention in improving both reasoning processes and paranoia [35, 36].

However, the use of CBM to modify interpretations of material specifically relevant to paranoia and paranoid beliefs remains unexplored and CBM-pa was designed to fill this gap.

### Feasibility, double-blind randomised controlled trial

The current study is a feasibility, double-blind RCT of CBM-pa with patients who suffer from persistent, distressing paranoid symptoms. The CBM-pa intervention is delivered on a computer, set up by the researchers and, thereafter, is a self-directed, automated package, self-administered by the patient. The intervention uses ambiguous scenarios which could potentially be interpreted in a manner that reinforces paranoia, or instead could be interpreted in more benign way. While patients read these scenarios they are asked to complete experimental tasks (word completion and comprehension questions) which implicitly influence the interpretation that is actually made. Additional file 1: Figures S1a–h shows an example trial from the intervention. The intervention aims to reduce paranoid beliefs, paranoid symptoms and stress/distress, and will be evaluated in comparison to a text-reading control (see Additional file 1: Figure S1i). Both conditions will be conducted in addition to Treatment as Usual (TAU) which will be in the form of individualised combinations of medication and care coordination. This design directly evaluates the hypothesised ‘active ingredient’ (bias reduction) by using the control condition to match all other aspects of the adjunct intervention.

The main objective of this feasibility study is to test the integrity of the protocol in terms of length and feasibility. A secondary objective is a preliminary evaluation of efficacy. For this the primary outcome is the severity of paranoid symptoms. A third objective is the selection of primary outcomes (e.g. paranoid symptoms, interpretation bias and vulnerability to stress) for the subsequent trial based on consensus after presentation of results to the Steering Group. This decision will be informed by (1) observed effect sizes and (2) opinions on the most important outcome from qualitative interviews. The necessary withholding of information about group assignment might be a significant issue because heightened suspiciousness is an inherent feature of clinical paranoia.

Estimates of population variances of the main outcomes for future power calculations will be based on Browne [37], who suggests using the upper 80th percentile of confidence intervals around the estimates.

## Methods

The study has been approved by the London – City Road and Hampstead Research Ethics Committee on 26 February 2016 (reference: 16/LO/0071) and has been registered (Current Controlled Trials, ID: ISRCTN90749868). Amendments will be submitted to both the Ethics Committee and the Clinical Trials Register. Informed consent will be obtained from all participants. A Trial Steering Group (TSG) and LEAP (Lived Experience Advisory Panel) have been formed. The TSG also functions as a Data Monitoring Committee by assessing, at regular intervals, the progress of the study, participant safety, feedback and complaints, study milestones and, if relevant issues arise, whether to continue, modify, or stop the trial.

### Participants and study setting

The primary endpoints of this feasibility trial are factors that affect successful trial conduct, rather than measures of intervention effects. Hence, power analyses for intervention outcomes were not undertaken in advance. The study recruitment target is 60 participants, consistent with the widely accepted sample size of 20–40 participants for pilot studies [38, 39], allowing for some dropout. Assuming a follow-up rate of 70% or more, a one-sided 95% confidence interval for this key feasibility parameter will extend no more than 10% from the observed proportion. A minimum sample size of 30 is sufficient to obtain robust estimates of population variances for future power calculations [37, 38]. Therefore, recruiting 60 patients in this pilot trial should be sufficient to provide estimates of population variance on key outcomes.

Participants will be recruited from a range of local sources, including: Institute of Psychiatry, Psychology and Neuroscience (IoPPN) and South London and Maudsley (SLaM) research registers; SLaM NHS Foundation Trust services; service users’ networks and voluntary sector organisations. Patients will be screened and selected for invitation to participate by researchers according to the inclusion and exclusion criteria. The inclusion criteria are:Any diagnosis featuring clinically significant persecutory or paranoid symptoms, present for at least the preceding month. In order to be included in the study, participants had to score 3 or more on the Positive And Negative Syndrome Scale (*PANSS*) item 6 [40] of the positive symptoms scale and which measures ‘suspiciousness/persecution’. Paranoid symptoms were assessed over the telephone by a trained researcher. A score of 3 reflects ‘mild’ paranoid symptoms as expressed by ‘a guarded or even openly distrustful attitude’;Displaying a baseline interpretation bias. A link is sent to potential participants to complete a bias screening task online (or, for those without Internet access, participants are asked to come to the IoPPN and complete it using local laptops). The bias screening task is a shortened (eight-item) version of the *Similarity Rating Task* (*SRT*) [41] delivered using the on-line data collection software Qualtrics. Shortened versions have demonstrated adequate reliability in previous work [42]. The items used in this task were sourced by randomly selecting from the original CBM-pa training items used in sessions 1, 2 or 3. It was ensured that the items chosen were distinctive, and had an even number of yes/no correct responses. In the screening *SRT*, sentences reflecting non-paranoid (i.e. benign) and paranoid interpretations were denoted T+ and T−, respectively, and rated by participants on a 1–4 Likert scale (higher score = stronger endorsement). An interpretation bias screening score is calculated: T+ minus T−. Screening bias scores, therefore, range from +3 to −3 with positive and negative scores reflecting bias favouring nonparanoid and paranoid meanings, respectively. A bias score of 1 or below during the *SRT* at screening is necessary to be selected for the study. This cutoff has been adopted in order to exclude anyone showing a strong positive interpretation bias. The screening version of the *SRT* differed slightly from the baseline version, in that there were only eight *SRT* items and no foilsStable on all prescribed medication (including anti-psychotic) for at least the last 3 months and expected to be so for study durationAge range of 18–65 yearsCapacity to consent defined as the ability to use and understand information to make a decision, and communicate any decision made. This is assessed by a trained research assistant (CM) and a clinical psychologist (AT) according to the Mental Capacity Act [43]

Exclusion criteria are:Severe cognitive impairment, or illiteracyMajor physical illness (cancer, heart disease, stroke)Major substance or alcohol misuse, andCurrently receiving, or soon due to receive, a psychological therapy targeting the same psychological mechanisms as CBM-pa (paranoid beliefs), or having done so in the last 3 months

Psychological therapy is defined as five or more consecutive sessions with a trained therapist, either in an individual or group setting, for the purpose of alleviating symptoms arising from paranoia or related issues. Receipt of therapy for any other purpose (e.g. occupational or art therapy; counselling) will be assessed on a case-by-case basis, against the principle that eligibility requires any cognitive mechanisms targeted by therapy to be independent of those targeted by CBM-pa.

### Randomisation and blinding

We will conduct this study following Consolidated Standards of Reporting Trials (CONSORT) guidelines [44]. The King’s Clinical Trials Unit will conduct double-blind randomisation. CBM-pa is self-administered, allowing researchers to be blind to condition. Control and intervention are designed to appear procedurally identical. Blinding will be implemented by the creation of 60 unique, randomly labelled computer programmes which mask the assigned treatment arm from researchers. Should occasional instances of unblinding accidentally occur, these can be reported without jeopardising the status of the remainder of the sample. Participants and researchers will be asked to guess the assigned condition to evaluate the success of double-blinding at the end of all data collection. Adaptive randomisation by minimisation will be used that allocates subjects to the treatment group that best maintains balance in stratifying factors, such as: gender, severity of baseline paranoia measured by the *PANSS* item 6 [40], severity of interpretation bias measured by the *SRT* [41].

## Interventions

Participants will attend the Institute of Psychiatry, Psychology and Neuroscience, King’s College London, or the NIHR/Wellcome Trust King’s Clinical Research Facility, for six sessions and receive postal/telephone 1-and 3-month follow-ups (respectively at 4 and 12 weeks from end of last session). See Fig. 1 for the trial flow diagram.

**Fig. 1 Fig1:**
[figure not shown]
Trial flow diagram

Groups should be equalised on the expectation of benefit because the introduction to each trial arm is delivered by computer and standardised across the two conditions. Expectation of benefit will be assessed using the *Credibility and Expectancy Questionnaire* [45]. The intervention will be delivered on laboratory-owned laptops.

Qualitative interviews (*n* = 8) will be conducted after the end of quantitative data collection, providing an in-depth assessment of participants experience of the intervention, including potential side effects (e.g. unexpected emergence, rather than amelioration of paranoid thoughts).

### Treatment-as-Usual (TAU) + CBM-pa

We will record details of TAU received during the study period using a standardised template to record participants’ responses to a series of set questions about treatment received, including pharmacotherapy and any treatment changes. The first 10 participants consenting for access to notes will be used to assess feasibility of case-note data collection to record TAU.

#### CBM-pa procedure and item development

CBM-pa (see Additional file 1: Figures S1a-h) consists of 40 unique training items completed per session (duration 40 min plus midpoint break), for six weekly sessions, involving a total of 240 different items.

To maximise clinical relevance, the LEAP group developed over 100 examples of everyday situations drawn from their real experiences to be used as content for the six study intervention sessions. Training items were selected from these and further developed by the research team into the format required for use as a training item (see example given in Additional file 1). The items were arranged into six topic areas/categories of paranoia, namely:Physical harm (37 items): e.g. being poisoned, injured, threatened by terrorism, killed, etc.Social/interpersonal threat (87 items): e.g. being gossiped about, judged, disliked, dumped, firedMedical/paramedical/health care threat (19 items): e.g. being prescribed drugs with adverse effects, being conspired against by medical staff conspire against you, having one’s deoxyribonucleic acid (DNA) stolenThreat of persecution/spying (40 items): e.g. being stalked, spied on, followed, arrested by policeDelusions of reference/magical thinking (15 items): e.g. interpreting stimuli as personal messagesGeneral suspiciousness/distrust not relating to physical threat or persecution (42 items): e.g. being robbed, plagiarised, irritated by neighbours

Items were independently rated, according to their severity, by two clinical psychologists (EP, AT). The intra-class correlation coefficient for the severity ratings (ICC) was 0.992 (indicative of strong inter-rater reliability). Training items were distributed across sessions in terms of their mean severity ratings such that items become more severe from one session to the next, based on previous research findings suggesting this is more acceptable to participants with pre-existing negative biases [42].

A typical item is shown in Additional file 1: Figure S1b. Each item depicts an emotionally ambiguous situation, is interactive and involves participants reading three lines of text on a computer screen, then completing a missing word and answering a related question (yes/no). Both the word completion and the question encourage participants to interpret the ambiguity inherent in the situation in a manner that promotes helpful beliefs about themselves and others (see example given in Additional file 1: Figures S1a − h). Equal numbers of ‘yes’ and ‘no’ question responses are presented randomly to avoid participants developing a fixed response set. Word completions were unique (no repetitions) and constructed by removing all vowels, then reinstating one in cases where LEAP feedback indicated that the resulting difficulty level was too high. In response to further feedback from LEAP a ‘clue’ was created for each item by adding more letters to encourage the participant to try again following an incorrect response.

In order to reflect the increasing drill down towards core beliefs that is used in traditional cognitive therapies, sessions 1 and 2 are delivered using the word ‘thoughts’ (e.g. ‘You fly to a business meeting abroad. You plan to attend the guest reception but arrive 20 min late. Upon entering the reception you look around and *think* everyone looks…’); 3 and 4 using ‘assumptions’ (e.g. ‘You are running late for an appointment and rush to get to the bus stop on time. As you approach, gesturing for the bus to wait, you see the driver look in the mirror and pull away, smiling. You *assume* that the bus driver just…’) and 5 and 6 using ‘beliefs’ (e.g. ‘You are sitting at a bus stop when a group of teenagers walk over and light up their cigarettes. As you cough loudly, they throw the empty carton saying ‘smoking kills’ towards you and laugh. You *believe* that this is…’).

### Treatment-as-usual (TAU) + text-reading control

A computerised text-reading control will be given to those randomised to this condition (see Additional file 1: Figure S1i). The experience is identical to CBM-pa, but content omits the active ingredient: resolution of an emotionally ambiguous situation in a benign/non-paranoid manner. Instead control participants read and respond to factual material. Similarly to CBM-pa, training items were divided into six sessions of 40 items each. It was ensured that there are no obvious systematic differences between the control and intervention items (equal number of yes/no answers in each session, no word repetitions in the incomplete words, each item is three sentences long over three lines, topics are evenly distributed between each session).

The LEAP group reviewed all items to be used in the study intervention and control arm for readability and suitability and tested the software to be used in the study for acceptability.

## Outcome measures and timeline

The Standard Protocol Items: Recommendations for Interventional Trials (SPIRIT) diagram provides an overview of the measures used in the trial and their time points (see Fig. 2). To evaluate the optimum number of sessions, dose-response effects will be assessed by measuring paranoid symptoms and interpretation bias at each session (i.e. what ‘dose’ of interpretation bias training achieves the best reduction in paranoia) using the secondary outcome measures (see below). This will inform decisions about number of sessions for full trial.

**Fig. 2 Fig2:**
[figure not shown]
Standard Protocol Items: Recommendations for Interventional Trials (SPIRIT) diagram

### Primary outcomes

As the study is a feasibility evaluation of the CBM-pa intervention there is no single primary outcome measure. Instead, feasibility will be assessed on the basis of rates of recruitment, consent, dropout and follow-up. In addition, acceptability of randomisation will be examined, including the integrity of double-blinding. Qualitative interviews will be conducted after the end of quantitative data collection, using a purposively selected subsample of eight active-arm patients. Purposive selection will represent sample variation in the following priority order: gender, severity of paranoia, severity of bias, age and ethnicity. The aim is to explore acceptability, barriers to participation, promoting engagement and optimum form of delivery of the intervention.

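### The sampling list for the eight interviews omits attendance and withdrawal, so nothing secures the view of patients who left, although barriers and engagement are what the interviews are meant to explore

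*Protocol article*

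**What the plan says.** Under Primary outcomes, the protocol article plans interviews "using a purposively selected subsample of eight active-arm patients". The selection rule is explicit and ranked. In order of priority, the characteristics to be varied are "gender, severity of paranoia, severity of bias, age and ethnicity". The purpose follows directly: "The aim is to explore acceptability, barriers to participation, promoting engagement and optimum form of delivery of the intervention". On timing, "Qualitative interviews will be conducted after the end of quantitative data collection".

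The Interventions section, after Fig. 1, gives the same number and timing and describes the interviews as "providing an in-depth assessment of participants experience of the intervention, including potential side effects". The Background subsection on the feasibility design adds a further use: patients' opinions from the interviews will help choose the primary outcome of the later trial.

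Dropout also has a formal place in the plan: "feasibility will be assessed on the basis of rates of recruitment, consent, dropout and follow-up". The Statistical analysis section gives proportions with confidence intervals for these rates and says that rates and characteristics of dropout will be explored. Neither that section, the second description of the interviews, nor the Qualitative analysis section says that patients who left will be sought for interview.

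**The concern.** All five listed characteristics describe who the patient is. None describes how far the patient took part: sessions attended, withdrawal or completion. The list therefore does not set out to vary the feature most directly tied to two of the stated aims, barriers and engagement. Dropout will be counted, but no step makes sure that anyone who dropped out is asked why.

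The article itself fixes the list and its order, so this is a stated design choice and not a detail left to a fuller document.

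At stake is qualitative information that the full trial would need. The Background subsection notes that withholding allocation may be a particular problem in suspicious patients, and the Interventions section names the unexpected emergence of paranoid thoughts as a possible side effect. If either leads patients to leave, those who stayed can say less about it.

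**Working it through.** **Inputs from the protocol article**
- 60 patients (Participants and study setting), allocated 50:50 (Abstract), so about 30 in the active arm.
- 8 interviewees, active arm only (Primary outcomes).
- Follow-up assumed to be 70% or more (Participants and study setting), so at most 30% lost.

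**Assumptions**
- Loss to follow-up stands in for leaving the intervention. The article gives no figure for session completion. The two differ: a patient can finish all six sessions and miss the later postal or telephone follow-up.
- 70% is a floor, so smaller losses are shown as well: 9, 6 and 3 leavers out of 30 (30%, 20%, 10%).
- The relative reachability of leavers is not in the article. Values of 1, 0.5 and 0.25 are shown as a range.

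**The plan's own figure.** The article says that the one-sided 95% limit for follow-up lies within 10% of the observed proportion. With the normal approximation, 1.645 × √(0.7 × 0.3 / 60) = 0.097, so the statement reproduces. The present point does not depend on it.

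**Selection that ignores completion, equal reachability.** With d leavers out of 30:
- Expected leavers among the eight = 8 × d/30.
- Chance of none = C(30 − d, 8) / C(30, 8), where C(30, 8) = 5,852,925.

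Results:
- d = 9: expected 8 × 9/30 = 2.4; chance of none = 203,490 / 5,852,925 = 3.5%.
- d = 6: expected 1.6; chance of none = 735,471 / 5,852,925 = 12.6%.
- d = 3: expected 0.8; chance of none = 2,220,075 / 5,852,925 = 37.9%.

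**Leavers harder to reach.** Simulation of 20,000 draws of 8 from 30 without replacement, with each leaver given weight 0.5 or 0.25 against 1 for a completer:

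| Leavers of 30 | Equal reachability | Half as likely | A quarter as likely |
|---|---|---|---|
| 9 | 3.5% | 16% | 38% |
| 6 | 12.6% | 34% | 57% |
| 3 | 37.9% | 61% | 78% |

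Entries are the chance that no leaver is interviewed.

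**Why lower reachability is plausible.** Read patient by patient, interviews come after the 12-week follow-up. Someone who left after session 1 would then be approached about 5 + 12 = 17 weeks later. If the timing means the end of data collection for the whole trial, the gap could be longer. This supports showing the right-hand columns but does not establish any particular value.

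**The case against.** The strongest reply is that the list is neutral on completion. It draws on active-arm patients, and those who left are still active-arm patients. With 9 leavers and equal reachability, 2.4 are expected among the eight, which is already within the two or three one would ask for, and the chance of none is only 3.5%. The higher figures at 9 leavers need a reachability assumption with no source in the article. All of this stands. A reader might infer that the rule will mainly pick completers; the list alone does not support that.

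A reader might also infer that acceptability will be overstated. The documents do not support this either. Feasibility and acceptability are summarised by proportions that include dropout and follow-up, and these count leavers. The interviews yield themes, not a rate that could be shifted.

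Nor is the late timing a defect. The interviews are confined to the active arm, and the Data monitoring section links allocation to trial data only when all data collection is complete. Choosing active-arm patients earlier, for instance as they leave, could reveal allocation.

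The interviews also serve aims for which completers are well placed, such as form of delivery and opinions on outcomes. That limits how much of the sample should go to leavers. It does not explain why none is reserved for them. How patients are approached may be described in a fuller protocol, so the absence of outreach details is not held against the article. The ranked list, however, is stated in full.

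**Conclusion.** The point holds in a limited form. The ranked list leaves out attendance and withdrawal although the interviews address barriers and engagement, and no other section makes up for it. Leavers may be included, but only by chance.

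With equal reachability, the chance of missing them altogether is small if many leave and substantial if few do, and it rises in every case if leavers are harder to reach. At low dropout there are fewer reasons for leaving to discover, but deliberate selection is then needed more if any are to be heard. These figures rest on about 30 active-arm patients, on follow-up loss standing in for non-completion, and, beyond the first column of the table, on assumed reachability.

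The likely loss is in-depth reasons for leaving. No estimate, confidence interval or sample size is affected. This is a cheap improvement.

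**What to change.** Add completion status (missed sessions or withdrew, versus completed) high in the priority order. Seek about two or three of the eight interviewees from patients who missed sessions or withdrew and who agree to be contacted. Keep the interviews after the end of quantitative data collection, so that blinding is preserved.

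If too few such patients agree, report this and limit the qualitative conclusions on barriers and acceptability to completers.

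The cost is a change to one sentence and slightly less variety on the lowest-priority characteristics. No extra interviews are needed.
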